### PART 2: SCREENING INTERVIEW with PARENTS/GUARDIANS

| Selection criteria                                                                                                                                                   | Include | Exclude |                                                                         |
|----------------------------------------------------------------------------------------------------------------------------------------------------------------------|---------|---------|-------------------------------------------------------------------------|
| 1. Appropriate age
—Under five (aged 0 to less than 5 years)                                                                                                      | 1 = Yes | 2 = No  | 

 |
| 2. Fever or suspected fever                                                                                                                                          | 1 = Yes | 2 = No  | 

 |
| 3. Danger signs of severe disease? (Convulsions, severe weakness/lethargy, unable to feed, unable to stand/sit unsupported, vomiting everything, severe dehydration) | 1 = No  | 2 = Yes | 

 |
| If any answers are '2' from the EXCLUDE column, exclude from the study. If not, proceed to the next section.                                                  |         |         |                                                                         |

### PART 3: INFORMED CONSENT

| Selection criteria                                                                                                  | Include | Exclude |                                                                         |
|---------------------------------------------------------------------------------------------------------------------|---------|---------|-------------------------------------------------------------------------|
| 4. Willingness of caregiver to provide informed consent                                                             | 1 = Yes | 2 = No  | 

 |
| If any answers are '2' from the EXCLUDE column, exclude from the study. If not, proceed to the next section. |         |         |                                                                         |

|                                |                                                                                         |
|--------------------------------|-----------------------------------------------------------------------------------------|
| ASSIGN
STUDY NUMBER | 

 |
|--------------------------------|-----------------------------------------------------------------------------------------|

|                                                                                                                                                                                                     |                                                                                                                                                                                                                                                                                                                                                                                                                                                                                                       |
|-----------------------------------------------------------------------------------------------------------------------------------------------------------------------------------------------------|-------------------------------------------------------------------------------------------------------------------------------------------------------------------------------------------------------------------------------------------------------------------------------------------------------------------------------------------------------------------------------------------------------------------------------------------------------------------------------------------------------|
| All criteria for study inclusion met?
1 = Yes
2 = No If no, exclude from the study

 | Date of enrollment

 

 

 

 
 
 day month year 
 |
|-----------------------------------------------------------------------------------------------------------------------------------------------------------------------------------------------------|-------------------------------------------------------------------------------------------------------------------------------------------------------------------------------------------------------------------------------------------------------------------------------------------------------------------------------------------------------------------------------------------------------------------------------------------------------------------------------------------------------|

Staff ID: Data entrant (1st): Data entrant (2nd):

[figure not shown][figure not shown][figure not shown][figure not shown][figure not shown]

[ ] [ ] [ ] [ ] [ ]

HCWA Study ID

## APPENDIX M. HEALTH WORKER COMMUNICATION ASSESSMENTS and PATIENT EXIT INTERVIEWS

**APPENDIX N. HEALTH WORKER COMMUNICATION ASSESSMENT****PART 1: CAREGIVER DETAILS**

|                                                                       |                                  |                                                                  |                                                           |
|-----------------------------------------------------------------------|----------------------------------|------------------------------------------------------------------|-----------------------------------------------------------|
| Health center code
[ ][ ]                                   | Patient ID code
[ ][ ] | Interviewer code
[ ][ ]                                | Date
[ ][ ] / [ ][ ] / [ ][ ]
day month year |
| 1. Number of patients brought by the caregiver today
[ ][ ] |                                  | 2. Number of eligible children being seen today
[ ][ ] |                                                           |

**PART 2: CAREGIVER DEMOGRAPHIC INFORMATION**

|                                                                                                                                                                                                                                                                                                                                |                                                             |
|--------------------------------------------------------------------------------------------------------------------------------------------------------------------------------------------------------------------------------------------------------------------------------------------------------------------------------|-------------------------------------------------------------|
| 1. Caregiver age
[ ][ ] years                                                                                                                                                                                                                                                                                        | 2. Caregiver gender
1 = Male
2 = Female
[ ] |
| 3. Been to this health centre before?                                                                                                                                                                                                                                                                                   | 1 = Yes
2 = No
[ ]                                    |
| 3. Originally from this area?                                                                                                                                                                                                                                                                                           | 1 = Yes
2 = No
[ ]                                    |
| 5. Highest level of education or qualification achieved
0 = None      4 = Diploma      77 = Other
1 = Primary (P1 — P7)      5 = Bachelor's degree
2 = Secondary (S1 — S6)      88 = Don't know
3 = Certificate      99 = Refused to answer                                                                 |                                                             |
| 5. Employment
0 = Not employed      2 = Commercial farmer      77 = Other
1 = Teacher      3 = Brew alcohol
2 = Nurse      4 = Market vendor
3 = Member of village health team      5 = Shop keeper      88 = Don't know
1 = Peasant farmer      6 = Transport(Driver/rider)      99 = Refused to answer |                                                             |

**PART 3: PATIENT DEMOGRAPHIC INFORMATION**

|                                                                                                                                                                                                                                                                                |                                                   |
|--------------------------------------------------------------------------------------------------------------------------------------------------------------------------------------------------------------------------------------------------------------------------------|---------------------------------------------------|
| 1. Age of child enrolled
[ ][ ] years                                                                                                                                                                                                                                | 2. Gender
1 = Male
2 = Female
[ ] |
| 3. What problems does the child have? (list all mentioned by the caregiver)
1 = None      9 = Diarrhoea
2 = Cough      10 = Skin infection
3 = Flu      77 = Other
4 = Not eating
5 = Vomiting
6 = Weak (not playing)
7 = Convulsions
8 = Fever |                                                   |

## APPENDIX O. HEALTH WORKER COMMUNICATION ASSESSMENT PATIENT EXIT INTERVIEW

|                                                                     |                         |                              |                                                                |                                                              |
|---------------------------------------------------------------------|-------------------------|------------------------------|----------------------------------------------------------------|--------------------------------------------------------------|
| Health Center ID
[ ] [ ]                                  | HW ID
[ ] [ ] | Patient ID
[ ] [ ] | Interviewer ID
[ ] [ ]                               | Date
[ ] [ ] / [ ] [ ] / [ ] [ ]
day month year |
| 1. Number of patients brought by the caregiver today [ ] [ ] |                         |                              | 2. Number of eligible children being seen today [ ] [ ] |                                                              |

|                                                                                                                                                                                       |                        |                        |
|---------------------------------------------------------------------------------------------------------------------------------------------------------------------------------------|------------------------|------------------------|
| 1. What was the reason you came here today? (List, in mother's words, below)                                                                                            |                        |                        |
|                                                                                                                                                                                       |                        |                        |
| 2. Did you feel you were able to discuss this problem fully with the health worker?                                                                                            | 1 = Yes                | [ ] [ ]                |
|                                                                                                                                                                                       | 2 = No                 | [ ] [ ]                |
| 3. Do you think that the health worker understood how important this problem is to you and your child?                                                                         | 1 = Yes                | [ ] [ ]                |
|                                                                                                                                                                                       | 2 = No                 | [ ] [ ]                |
| 4. Did you feel that the health worker was listening to you with full attention?                                                                                               | 1 = Yes                | [ ] [ ]                |
|                                                                                                                                                                                       | 2 = No                 | [ ] [ ]                |
| 5. Did the health worker give you enough information about why he thinks the child is experiencing the problem(s)?                                                             | 1 = Yes                | [ ] [ ]                |
|                                                                                                                                                                                       | 2 = No                 | [ ] [ ]                |
| 6. Do you agree with the health worker's opinion about the problem?                                                                                                            | 1 = Yes                | [ ] [ ]                |
|                                                                                                                                                                                       | 2 = No                 | [ ] [ ]                |
| 7. Do you feel the health worker could have done more to investigate the problem of your child today?                                                                          | 1 = Yes                | [ ] [ ]                |
|                                                                                                                                                                                       | 2 = No                 | [ ] [ ]                |
| 8. How satisfied were you with the treatment you were given? (Allocate category that fits best with response, check with mother)                                        | 1 = Very satisfied     | 3 = Somewhat satisfied |
|                                                                                                                                                                                       | 2 = Satisfied          | 4 = Not satisfied      |
|                                                                                                                                                                                       |                        | [ ] [ ]                |
| Did the health worker explain what this medicine will do?                                                                                                                      | 1 = Yes                | [ ] [ ]                |
|                                                                                                                                                                                       | 2 = No                 | [ ] [ ]                |
| Did the health worker help you to understand how the child should take this medicine?                                                                                          | 1 = Yes                | [ ] [ ]                |
|                                                                                                                                                                                       | 2 = No                 | [ ] [ ]                |
| Did the health worker help you to understand what to expect during the child's illness?                                                                                        | 1 = Yes                | [ ] [ ]                |
|                                                                                                                                                                                       | 2 = No                 | [ ] [ ]                |
| How confident do you feel that your child will get better if you follow the health worker's advice? (Allocate category that fits best with response, check with mother) | 1 = Very confident     |                        |
|                                                                                                                                                                                       | 2 = Somewhat confident |                        |
|                                                                                                                                                                                       | 3 = Not confident      | [ ] [ ]                |
| Overall, how did the health worker make you feel? (Allocate category that fits best with response, check with mother)                                                   | 1 = Very happy         |                        |
|                                                                                                                                                                                       | 2 = Somewhat happy     |                        |
|                                                                                                                                                                                       | 3 = Unhappy            | [ ] [ ]                |
| Overall, how welcome did you feel at this health centre from start to finish?                                                                                                  | 1 = Very welcome       | 3 = Somewhat welcome   |
|                                                                                                                                                                                       | 2 = Welcome            | 4 = Unwelcome          |
|                                                                                                                                                                                       |                        | [ ] [ ]                |
| Next time your child is sick, will you come back to here?                                                                                                                      | 1 = Yes                | [ ] [ ]                |
|                                                                                                                                                                                       | 2 = No                 | [ ] [ ]                |
| Overall, how satisfied were you with the consultation today?                                                                                                                   | 1 = Very satisfied     | 3 = Somewhat satisfied |
|                                                                                                                                                                                       | 2 = Satisfied          | 4 = Not satisfied      |
|                                                                                                                                                                                       |                        | [ ] [ ]                |
| Do you have any additional comments about this consultation with the health worker?                                                                                            |                        |                        |
|                                                                                                                                                                                       |                        |                        |

[figure not shown][figure not shown][figure not shown][figure not shown][figure not shown]

[ ] [ ] [ ] [ ] [ ]

IDI Study ID

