### **5.3.2. Health worker communication assessments + patient exit interviews**

We aim to conduct communication assessments with at least one health worker in each health facility in both the HFI and standard care arms (10 in each arm). Each communication assessment will consist of at least three, and no more than five, health worker/caregiver interaction records. The communication assessments will be conducted immediately before and up to 6 weeks after the HFI training in patient-centered services, and then approximately six months following the training for a total of three cycles. The same health workers will be assessed at each time point to evaluate for changes over time. We will evaluate approximately 20-25 health workers chosen by convenience sampling. Therefore conducting up to 125 health worker/caregiver interactions in each time period; 375 in total, depending on the number of health workers and patients available at the health centers on the days of the study. One health worker will be chosen from each of the level II health centers, and 1-2 health workers will be chosen from each of the level III centers. Exit interviews will be conducted with all consenting caregivers who participated in the assessments, up to a maximum of 125 interviews at each time point, 375 in total.

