## **5.5. HEALTH WORKER COMMUNICATION ASSESSMENTS AND PATIENT EXIT INTERVIEWS**

We plan to conduct communication assessments with health workers from both the HFI and standard care arms. The purpose of the assessments is to evaluate and compare the communication between health workers and patients immediately before and after HFI training in ‘communicating with patients’ and then during the study period. Health worker/caregiver interactions during consultations will be audiotaped and assessed using a validated measurement methodology, the Measurement of Patient-Centered Communication (MPCC) (Appendix I). The MPCC scores assessments according to three elements of patient-centered communication: 1) exploring the disease and the illness experience, 2) understanding the whole person, and 3) finding common ground [44]. In addition to the recorded interactions, consenting caregivers will be interviewed immediately on exit from the consultation to give their view of the quality of the interaction with the health worker. The purpose of the interviews is to determine the level of satisfaction of caregiver with the health facility visit.

Health workers from both the HFI and standard care arms available on the day of the communication assessment will be selected using convenience sampling, and invited to participate. At least one health worker from each facility, will be included. At least three interactions, and up to five interactions, will be recorded with each health worker. Written informed consent to conduct the assessments will be obtained from health workers before beginning (Appendix J) as outlined in section 8.2. Demographic information on the health worker will then be obtained (Appendix K).

Once a health worker has been selected and provided informed consent, caregivers who will have a consultation with that health worker will be selected using convenience sampling from the available patients visiting the health center on the day of the health worker communication assessment.

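### Three of the five graded exit-interview ratings are categorised by the interviewer and then checked with the caregiver, with no masking described and no verbatim answer kept; the caregiver should choose from options presented to her in the same way for all five.

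*Supplement*

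**What the plan says.** Section 5.5 gives the purpose of the exit interview as to "determine the level of satisfaction of caregiver with the health facility visit". Consenting caregivers "will be interviewed immediately on exit from the consultation". Section 5.3.2 places the assessments "in both the HFI and standard care arms (10 in each arm") and sets three rounds: before the patient-centred services training, up to six weeks after it, and about six months after it.

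Appendix O has 15 closed items: ten yes/no and five graded. The graded ones are not all collected in the same way:

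- Item 8, satisfaction with treatment (four categories): "Allocate category that fits best with response, check with mother".
- "How confident do you feel that your child will get better if you follow the health worker's advice" (three categories): same instruction.
- "Overall, how did the health worker make you feel" (three categories): same instruction.
- "Overall, how welcome did you feel at this health centre from start to finish" (four categories): no instruction.
- "Overall, how satisfied were you with the consultation today" (four categories): no instruction.

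The form has two open fields, one for the reason for the visit and one for closing comments. None sits beside the three allocated items. Section 7.1 sends categorical exit-interview data to chi-square or Fisher's exact tests at a two-sided 0.05 level. Section 7.2 has the audio recordings dual-coded; no second coding is described for the exit interview.

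**The concern.** On the three allocated items the caregiver answers freely, the interviewer turns that answer into a category, and the caregiver is then asked to confirm it. The instruction does not say that she is offered the alternatives. The step that needs judgement, choosing between neighbouring grades such as 'very satisfied' and 'satisfied', comes first and belongs to the interviewer.

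These are subjective outcomes compared between arms and rounds. If the interviewer knows which facility and round she is in and expects the trained workers to do better, borderline answers may be coded upwards more often in the HFI arm after training. A chi-square or Fisher test cannot tell such a shift from a real improvement. With no verbatim answer and no second coding, it could not be found or corrected afterwards. The two ways of collecting graded answers also make the five ratings harder to compare with one another, and the plan gives no reason for the difference.

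**Working it through.** **1. The plan's own count.** Section 5.3.2 gives 20-25 health workers and 3-5 interactions each per round. Maximum: 25 × 5 = 125 per round, and 125 × 3 = 375 in total. Both stated figures reproduce. Minimum: 20 × 3 = 60 per round, 180 in total.

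**2. Items affected.** Graded items: 5. With the allocation instruction: 3. Of those three, only item 8 is a satisfaction rating.

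**3. Interviews in which the feared shift could arise.** Coding up in favour of training concerns the HFI arm in the two post-training rounds. With equal arms that is at most 375 × 1/2 × 2/3 = 125 interviews.

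**4. What the documents say about awareness.** The round follows from the visit schedule. No section states that interviewers know the arm. It is inferred from three things: interviews take place at the facility, the form records health centre and health worker, and no masking is described. Appendix U, Part 2 also has the study team administer an HFI-only section in a later instrument.

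**5. Illustrative size, item 8 only.** Neither input is in the documents; both are assumptions.

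Shift in share 'very satisfied' = (share who would answer 'satisfied') × (share of those coded up)

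- Low: 0.30 × 0.10 = 0.03, or 3 points
- High: 0.50 × 0.30 = 0.15, or 15 points

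On at most 125 interviews this is 0.03 × 125 ≈ 4 to 0.15 × 125 ≈ 19 answers moved. The check with the caregiver is given no corrective effect, so for a given share of answers coded up at the first step this is the worst case. The other two allocated items have three categories and different labels, so the figures do not carry over to them.

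**6. What such a shift would do to one between-arm test.** Suppose, to simplify, that everyone not 'very satisfied' answers 'satisfied'. The true top-category shares are then 0.70 (low case) and 0.50 (high case) in both arms. Normal approximation, two-sided 0.05, clustering ignored:

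P(significant in favour of HFI) = Φ[(d − 1.96·√(2p̄(1−p̄)/n)) / √((p₁(1−p₁)+p₂(1−p₂))/n)]

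| n per arm | p₁ → p₂ | d | Calculation | Result |
|---|---|---|---|---|
| 62 | 0.70 → 0.73 | 0.03 | (0.03 − 1.96 × 0.0811)/0.0810 = −1.59 | 5.6% |
| 62 | 0.50 → 0.65 | 0.15 | (0.15 − 1.96 × 0.0888)/0.0878 = −0.27 | 39% |
| 30 | 0.70 → 0.73 | 0.03 | (0.03 − 1.96 × 0.1166)/0.1165 = −1.70 | 4.4% |
| 30 | 0.50 → 0.65 | 0.15 | (0.15 − 1.96 × 0.1276)/0.1262 = −0.79 | 21% |

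Here n = 62 is 125 split evenly and n = 30 is 60 split evenly. With no differential coding the reference value in that direction is 2.5%. At the low end little happens; at the high end a false finding becomes quite likely.

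**The case against.** Several points on the other side stand.

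- **The caregiver confirms the category.** The instruction has two halves, and a reader who sees only the first might infer that the interviewer alone sets the rating. The form does not say that. How far a caregiver would correct a proposed category cannot be known from the documents, so the check counts as a real but incomplete safeguard.
- **Knowledge of arm is not stated.** A reader might take it as fact that interviewers are unblinded. It is likely but inferred. Section 5.1 gives the work to a field team separate from ACT PRIME, which weakens any motive to favour the intervention. Section 6.2 promises task-specific interviewer training and SOPs; these are not shown and may say how options are presented.
- **The item closest to the stated purpose is not allocated.** A reader might infer that the satisfaction result as a whole is compromised. Only item 8 among the allocated items rates satisfaction, and the overall satisfaction item on the same form is free of the instruction.
- **Consequences are limited.** Table 4.1 assigns the exit interview to the process evaluation only. Communication is also measured from dual-coded recordings, and ACT PRIME measures patient satisfaction itself.
- **Open answer, coding and confirmation is a defensible method** where caregivers are unused to graded scales, and reading out options has a cost of its own (see the fix).

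What does not fall away is the uneven handling of five similar items on one form, the interviewer's discretion on three of them, and the lack of any record from which a shift could be detected.

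**Conclusion.** The point holds as a modest, avoidable weakness in the instrument. Three of five graded ratings pass through the interviewer's judgement before the caregiver confirms them, no masking is described, and nothing verbatim is kept.

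That such a shift will occur, or how large it would be, cannot be concluded from the documents. The 3-15 points are an illustration. They rest on two assumed shares, on coding up in the HFI arm only, and on the caregiver's check having no effect. They apply to item 8 in at most 125 post-training HFI interviews. Reading them as the expected bias, or applying them to all 375 interviews or all three items, would go beyond what the plan supports.

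**What to change.** In Appendix O, replace the allocation instruction, and add the same line to the two ratings that have none: *Read out all response options in the same fixed order (or show the response card) and record the option the caregiver chooses; do not suggest one.* Use it identically in both arms and in all three rounds, and cover it in interviewer training.

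The cost is one line of wording and a training point. There are two downsides. A fixed list can produce an order effect, for instance from the most favourable option coming first; the list is the same in both arms, so this should bear on the level of the ratings more than on the comparison. Caregivers unused to graded options may also need slightly more explanation. The change takes the choice of category away from the interviewer, but it does not mask her.

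If the team also wants the caregiver's own words, a short text line must be added beside the items, because none exists there now. In the analysis, use the overall satisfaction item as a cross-check: a gain on item 8 that it does not share should be read with caution. It is the less exposed item, though not a perfect standard, since the form does not say how its category is obtained.
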